Imaging is a powerful, yet underused, diagnostic tool that can be used to identify muscles with trigger points [15]. Ultrasound and magnetic resonance imaging (MRI) are both commonly used clinically to evaluate soft tissues [16-18]. Ultrasound is a noninvasive imaging technique with minimal contraindications that provides real-time assessments of soft tissue, including muscles and fascia [19]. In particular, ultrasound shear wave elastography (SWE) demonstrates high diagnostic accuracy in capturing abnormal biomechanical properties of myofascial tissue [15]. MRI is often regarded as the gold standard for evaluating soft tissues due to its ability to provide superior contrast, high resolution, and multiplanar images [18]. Previous studies have shown promise using T1 signal intensity and T2 mapping to detect structural alterations in trapezius muscles in women with migraines [20-22]. To build on previous foundational work, further research is needed to examine the diagnostic capabilities of both ultrasound and MRI within the same sample and to expand imaging approaches for identifying trigger points in the foot and ankle.

The primary aim of this proposed study is to develop a diagnostic imaging biosignature of myofascial pain to differentiate individuals with plantar heel pain from those with other kinds of foot pain (specifically insertional Achilles tendinopathy) and from matched pain-free controls. We hypothesize that a diagnostic biosignature, which uses both advanced ultrasound and MRI to quantify biochemical (muscle and fascia T1ρ), biomechanical (muscle SWE and fascia strain), and structural (muscle fat fraction and fascia thickness) tissue properties, will more accurately identify myofascial pain in the foot and ankle than a single imaging biomarker alone. We will also explore the potential of composite biosignatures that combine multiple imaging biomarkers with psychological factors, such as kinesiophobia, to provide a more comprehensive assessment. The development of a diagnostic biosignature may provide novel mechanistic insights into myofascial pain and offer a framework to facilitate the diagnosis of myofascial pain contributing to plantar heel pain.

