The physical therapist will palpate within the 5 zones to determine if a trigger point is present and mark the tautest band using a waterproof marker in a cross shape in each zone. This approach allows for the same locations to be assessed with ultrasound imaging and MRI. Trigger point identification will follow the gold standard diagnostic criteria established by Simons [54], who defines a trigger point as a taut band of skeletal muscle that is tender to palpation. The physical therapist will apply constant pressure with palpation for 5 seconds on the most tender taut band in each of the 5 zones, with a 20-second rest between each spot. Participants will be asked whether the pressure reproduces the same heel pain [54] and whether the pain is felt locally at the site of palpation or referred to another area [10] at each site. For comparison of imaging outcomes between trigger points and healthy tissue, at least 1 of the 5 marks will indicate healthy tissue using the same cross shape. Imaging researchers will remain blinded to the trigger point versus healthy tissue identification to ensure unbiased image acquisition.

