### Ultrasound Imaging

Ultrasound imaging will be performed by a physical therapist experienced in ultrasound imaging of the foot and ankle. To provide consistent positioning across the ultrasound and MRI scans, the participant will be in the prone position with the knee flexed to 15° and a strap around the ball of the foot applying slight pressure to maintain the ankle in a slightly plantarflexed position (approximately 20°). This ankle position replicates the 1.5-inch lift under the heel provided during the MRI. Ultrasound imaging will be acquired using the ACUSON Sequoia Ultrasound System (Siemens Healthineers). For SWE, a 10L4 linear array transducer (2.9-9.9 MHz) will be positioned parallel with the muscle fibers, centered over the 5 marks identified during the clinical examination. Because the plantar fascia lies immediately superficial to the flexor digitorum brevis, its shear wave speed will also be captured. In addition, as an exploratory measure, the transducer will also be positioned parallel with the Achilles tendon to capture the region immediately proximal to the calcaneus. A standoff pad will be used for Achilles tendon and abductor hallucis muscle imaging to allow for a similar imaging depth as the calf muscles, which have a greater amount of superficial adipose tissue. Three images per location will be collected. To quantify shear wave velocity, a custom MATLAB code will be used to allow for the selection of the tissue region of interest, with analysts blinded to the overlay of the shear wave velocity map. The average of the 3 replicates will be used to estimate a representative shear wave velocity for that tissue [64].

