The thickness of the plantar fascia will be measured using the maximum of 2 B-mode images, a long-axis and a short-axis view, at the insertion to the calcaneus. For the plantar fascia strain, an 18L6 linear array transducer (5.5-18 MHz) will be positioned parallel with the plantar fascia for a long-axis view. A cine loop will be collected while the participant’s great toe is passively extended from neutral to the end range of motion over 5 seconds. Simultaneously, a video of the foot will be captured on a tablet camera placed approximately 1 foot medial to the participant’s ankle, with the foot centered in the video frame and the screen positioned at a 90° angle relative to the floor. This passive range of motion task and imaging protocol will be repeated 3 times. A nonrigid image registration–based strain estimator will be used to measure the accumulated displacement field in the fascia throughout the first toe passive extension task [65]. The displacement estimates will then be used to quantify the average shear and principal strains within the plantar fascia during the passive movement. The magnitude of toe extension will be quantified using Kinovea software (open-source, version 0.9.5; Joan Charmant).

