The IDEAL-IQ gradient-echo images will be used for marker identification and tissue segmentation, and will serve as the reference images for spatially registering the other MRI images to a common image-space. The ROIs will be delineated using the IDEAL-IQ images, guided by the locations of the fiducial markers that are superficial to the trigger points. Detailed MRI scan parameters for the foot and lower leg, respectively, are provided in Tables S1 and S2. The corresponding ROIs will then be used to measure T1ρ, T2*, perfusion fraction, and pseudo-perfusion from IVIM, as well as fat–water fractions. Measurements from each ROI will include the mean, median, and SD. Quantitative maps of fat–water fraction and T2* will be automatically generated by the scanner using the IDEAL-IQ sequence, while voxel-wise parametric maps for T1ρ, T2, and IVIM will be produced using in-house software.

Qualitative image assessments will be performed by a radiologist to exclude differential diagnoses for plantar heel pain and to confirm accurate identification of leg and foot muscles.

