### Statistical Analysis

#### Data Analysis

In the statistical analysis, quantitative measures will be summarized with means, SDs, and quantiles, and categorical measures, including the presence of trigger points (trigger points vs healthy tissue), will be summarized with counts and percentages. Data will be described for 3 calf muscles (medial gastrocnemius, lateral gastrocnemius, and medial soleus) and 2 foot muscles (abductor hallucis and flexor digitorum brevis).

The primary study aim is to examine the diagnostic performance of 20 candidate biomarkers (biomechanical, biochemical, and structural) in distinguishing between tissue with and without myofascial pain. Performance will be quantified with the area under the receiver operating characteristic curve (ROC AUC), pooled over the 5 muscle groups assessed on each participant for imaged metrics and trigger points. Five-fold cross-validation will be used to estimate predictive performance, and bootstrap resampling applied to obtain 95% CIs. Participants will be treated as the sampling units in cluster cross-validation and bootstrap sampling algorithms to account for repeated muscle measurements in each participant. To identify the most promising biomarkers and account for multiple comparisons, false discovery rates will be computed with the method of Benjamini and Hochberg to rank the biomarkers in order of diagnostic performance [73]. Up to 5 top-performing biomarkers will be selected to constitute a single biosignature to achieve a target AUC >0.7, sensitivity >60%, and specificity >60%.

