#### Sample Size

The target sample size of 50 individuals with plantar heel pain, 25 individuals with insertional Achilles tendinopathy, and 25 pain-free controls was chosen to provide a 95% CI half-width of 0.10 for an AUC of 0.70. This calculation assumes 5 muscle measurements for each participant, an intraclass correlation coefficient of 0.5 among them, and an overall active trigger point prevalence of 36% in individuals with plantar heel pain [10,74]. Further assuming that the 20 candidate biomarkers have AUCs uniformly distributed from 0.5 to 0.8, the study will have at least 85% power to obtain a biosignature meeting the desired AUC threshold.

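### Blinding is stated only for the trigger-point label at image acquisition; masking to diagnosis group is not stated, which leaves reader-dependent measures, chiefly fascia thickness, unprotected

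*Protocol article*

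**What the plan says.** Under Trigger Point Identification, the article states that "Imaging researchers will remain blinded to the trigger point versus healthy tissue identification to ensure unbiased image acquisition". All marks have the same cross shape, and at least one of the five is healthy tissue.

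Under Ultrasound Imaging, shear-wave regions are selected "with analysts blinded to the overlay of the shear wave velocity map". This is the only masking stated for reading. For fascia thickness the same section says "The thickness of the plantar fascia will be measured using the maximum of 2 B-mode images", taken at the calcaneal insertion, and mentions no masking. Fascia strain comes from a registration-based estimator, also with no masking mentioned.

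Under MRI, "The ROIs will be delineated using the IDEAL-IQ images, guided by the locations of the fiducial markers". The same IDEAL-IQ sequence yields the fat-fraction map, which the scanner generates. Separately, "Qualitative image assessments will be performed by a radiologist to exclude differential diagnoses for plantar heel pain"; no masking is mentioned for that read either.

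The Introduction sets the aim at group level, to "differentiate individuals with plantar heel pain from those with other kinds of foot pain" and from pain-free controls. The Data Analysis section works at site level: it is about "distinguishing between tissue with and without myofascial pain", with the AUC pooled over five muscles per participant. The Sample Size section assumes "an overall active trigger point prevalence of 36% in individuals with plantar heel pain" and gives no prevalence for the two control groups.

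**The concern.** The blinding statement offers label masking as the protection against bias. Label masking prevents a reader from treating one mark on a foot differently from another mark on the same foot. It does not prevent a reader who knows the diagnosis from treating every image of a plantar heel pain participant differently from every image of a control.

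The second kind of bias matters for two reasons. Group is itself what the biosignature is meant to separate. And because the AUC is pooled over muscles from all participants, many of its positive-versus-negative comparisons are between people. If positive sites are concentrated in the plantar heel pain group, a systematic group difference in reading becomes apparent site-level accuracy. Resampling by participant, as planned, handles clustering but cannot remove measurement bias.

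Fascia thickness is the clearest case. It is a caliper-type judgement, it is named in the abstract among the primary imaging outcomes, and as described it gives one value per foot. Set against muscle-level labels, such a measure can discriminate only between participants, which is where group-aware reading acts.

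**Working it through.** The plan gives no figure on this point, so there is none to reproduce. Two quantities were worked out: how much group reveals about the label, and how far a group-aware reading shift would move the AUC.

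**Inputs**
- From the article: 50 plantar heel pain participants and 50 controls (25 + 25), five muscles each, so 250 sites per side; prevalence 36% in plantar heel pain; AUC target above 0.7; planned CI half-width 0.10.
- Assumed, because the article does not give them: control prevalence *c*, from 0% to 36%; a reading shift *d* of 0.2 to 0.5 SD in plantar heel pain images only, with normally distributed values of equal variance and no true signal.

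**Step 1. Group as a classifier of the label**

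Sensitivity = 0.36/(0.36 + *c*). Specificity = (1 − *c*)/((1 − *c*) + 0.64). AUC = (sensitivity + specificity)/2.

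| Control prevalence *c* | Sensitivity | Specificity | Group-only AUC |
|---|---|---|---|
| 0% | 1.00 | 0.61 | 0.81 |
| 5% | 0.88 | 0.60 | 0.74 |
| 10% | 0.78 | 0.58 | 0.68 |
| 20% | 0.64 | 0.56 | 0.60 |
| 36% | 0.50 | 0.50 | 0.50 |

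Group alone passes 0.7 only if control prevalence is about 8% or less (0.704 at 8%, 0.694 at 9%).

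**Step 2. Spurious AUC of a null marker**

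Let *w1* be the share of positive sites that lie in the plantar heel pain group (the sensitivity above) and *w0* the share of negative sites that do (1 − specificity). A positive and a negative site from the same side compare at 0.5; from opposite sides they compare at Φ(*d*/√2) or its complement. Summing the four cases gives:

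AUC = 0.5 + (Φ(*d*/√2) − 0.5) × (*w1* − *w0*).

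Φ(0.2/√2) = 0.556 and Φ(0.5/√2) = 0.638.

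| *c* | *w1* − *w0* | *d* = 0.2 | *d* = 0.5 |
|---|---|---|---|
| 0% | 0.610 | 0.53 | 0.58 |
| 10% | 0.367 | 0.52 | 0.55 |
| 20% | 0.198 | 0.51 | 0.53 |
| 36% | 0 | 0.50 | 0.50 |

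For control prevalences of 0% to 10%, a null marker would therefore show an AUC of 0.52 to 0.58, an inflation of 0.02 to 0.08. The inflation shrinks to nothing as control prevalence approaches 36%.

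**Step 3. Which measures leave room for reader judgement**
- Fascia thickness: taken by a reader from two B-mode views, with no stated safeguard. Most exposed.
- MRI regions: tied to fiducial markers, with a length matched to the 1.5 cm marker (Alterations to Study After Initiation). Fat-fraction and T2* maps come from the scanner. Some discretion remains in delineation.
- Fascia strain: computed by image registration; discretion is confined to choosing the region.
- Shear-wave speed: region chosen without sight of the values, then averaged over three images. Least exposed.

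**The case against.** The strongest reply is that the article is silent on group masking and does not deny it. It condenses a fuller protocol, no passage says that readers know the group, and the term imaging researchers may include those who read the images. This stands as far as it goes: a reader might infer that the image readers are unmasked, and the documents do not support that. What they do support is that the blinding statement fixes its own scope (the label) and purpose (acquisition), and that this scope does not address group.

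A second reply is that group does not give the label away. This also stands against the tempting stronger reading that group largely reveals it. At the article's own 36%, 64% of plantar heel pain sites are negative, so the best guess for any single site is healthy in either group, and group adds nothing to raw classification accuracy. Control prevalence is unknown. Moreover, the 36% refers to active trigger points, whereas the examination defines a trigger point as a tender taut band, which could also be found in controls. But the endpoint is the AUC, not raw accuracy, and the AUC does respond to group whenever prevalence differs between groups.

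A third reply is that an inflation of at most 0.08 lies below the planned half-width of 0.10 and would not lift a null marker to 0.7. True, and the shift itself is assumed. However, a confidence interval describes sampling error and does not absorb bias. Ranking 20 candidates and keeping up to five could also favour the markers that depend most on the reader.

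Finally, because region drawing and fat fraction share an acquisition, a reader might infer that the analyst sees fat fraction while drawing. The article does not say so.

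**Conclusion.** The point holds in limited form. As written, the blinding protects against label-aware handling at acquisition, and the overlay masking protects shear-wave region placement. Neither addresses knowledge of diagnosis group, so label blinding alone does not secure the reader-dependent measures. Plantar fascia thickness is the main exposure; MRI region placement and the strain region are secondary.

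Group is partly informative about the label: AUC 0.50 to 0.81 over an assumed control prevalence of 36% down to 0%. A null marker read 0.2 to 0.5 SD higher in plantar heel pain images would show about 0.52 to 0.58 if control prevalence is 0% to 10%, and less above that. Both the control prevalence and the shift are assumptions. The figures show that the bias could matter, not that it is present. This is a cheap improvement worth making, not a flaw that undermines the design.

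**What to change.** Export ultrasound and MRI files under random study codes and present them to readers in shuffled order. Extend the blinding statement so that everyone who measures fascia thickness, places shear-wave or MRI regions, or selects the strain region is masked to diagnosis group, symptoms and trigger-point label until the measurements are locked. If this is already practice, one sentence saying so is enough. Masking the sonographer to group is a further option where feasible, for example by withholding the screening record, but the main protection does not depend on it.

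The cost is file recoding and one sentence of protocol text, with no extra staff. The downside is re-reading any images already measured by someone who knew the group. With 55 of 100 participants enrolled by November 2025, that could affect part of the data, but stored images can be re-read without recalling participants.

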#### Pressure Pain Threshold Test

Following the completion of ultrasound and MRI, a pressure pain threshold test will be conducted using a pressure algometer (Somedic Algometer Type II) on each of the 5 previously marked locations on the leg and foot [56-60]. The algometer will be positioned perpendicularly to these sites, and pressure will be consistently applied downward at a constant rate of 50 kPa/s [61,62] using a 1-cm^2^ round rubber tip probe. Participants will be instructed to press a handheld button at the moment they first perceive the pressure sensation as painful, defined as anything greater than 0/10 on the NRS [63]. Three measurements will be taken per site, with at least 30 seconds between repetitions to reduce temporal summation effects. Participants with even and odd ID numbers will be tested in different sequences of muscle groups to minimize order effects.

### Ultrasound Imaging

Ultrasound imaging will be performed by a physical therapist experienced in ultrasound imaging of the foot and ankle. To provide consistent positioning across the ultrasound and MRI scans, the participant will be in the prone position with the knee flexed to 15° and a strap around the ball of the foot applying slight pressure to maintain the ankle in a slightly plantarflexed position (approximately 20°). This ankle position replicates the 1.5-inch lift under the heel provided during the MRI. Ultrasound imaging will be acquired using the ACUSON Sequoia Ultrasound System (Siemens Healthineers). For SWE, a 10L4 linear array transducer (2.9-9.9 MHz) will be positioned parallel with the muscle fibers, centered over the 5 marks identified during the clinical examination. Because the plantar fascia lies immediately superficial to the flexor digitorum brevis, its shear wave speed will also be captured. In addition, as an exploratory measure, the transducer will also be positioned parallel with the Achilles tendon to capture the region immediately proximal to the calcaneus. A standoff pad will be used for Achilles tendon and abductor hallucis muscle imaging to allow for a similar imaging depth as the calf muscles, which have a greater amount of superficial adipose tissue. Three images per location will be collected. To quantify shear wave velocity, a custom MATLAB code will be used to allow for the selection of the tissue region of interest, with analysts blinded to the overlay of the shear wave velocity map. The average of the 3 replicates will be used to estimate a representative shear wave velocity for that tissue [64].

The thickness of the plantar fascia will be measured using the maximum of 2 B-mode images, a long-axis and a short-axis view, at the insertion to the calcaneus. For the plantar fascia strain, an 18L6 linear array transducer (5.5-18 MHz) will be positioned parallel with the plantar fascia for a long-axis view. A cine loop will be collected while the participant’s great toe is passively extended from neutral to the end range of motion over 5 seconds. Simultaneously, a video of the foot will be captured on a tablet camera placed approximately 1 foot medial to the participant’s ankle, with the foot centered in the video frame and the screen positioned at a 90° angle relative to the floor. This passive range of motion task and imaging protocol will be repeated 3 times. A nonrigid image registration–based strain estimator will be used to measure the accumulated displacement field in the fascia throughout the first toe passive extension task [65]. The displacement estimates will then be used to quantify the average shear and principal strains within the plantar fascia during the passive movement. The magnitude of toe extension will be quantified using Kinovea software (open-source, version 0.9.5; Joan Charmant).

### MRI

To ensure spatial alignment between clinical examination, ultrasound imaging, and MRI, magnetic resonance–visible fiducial markers will be placed over the marked trigger points identified during clinical examination. MRI will be conducted using a 3T whole-body MRI (Signal Premier, GE Healthcare). Scanning will begin using an 8-channel foot-ankle receive RF coil (GE Healthcare, Waukesha) for imaging the foot, followed by a 32-channel flexible blanket array receive RF coil (GE Healthcare) for imaging the calf. Imaging will be performed on the affected side in participants with plantar heel pain and insertional Achilles tendinopathy, and on a single side in pain-free controls, with all participants scanned in the supine position with slight knee flexion and ankle plantar flexion to accommodate a 1.5-inch heel lift between the heel and the RF coil (approximately 20° of plantar flexion).

The imaging will include the following sequences: T2-weighted fast spin-echo sequences for T2 mapping and evaluation of inflammation and cysts [66]; zero echo time proton density sequences to detect bony abnormalities [67,68]; quantitative T1ρ imaging, which provides sensitivity to multiple features such as chemical exchange between extracellular water, macromolecules and pH [69,70]; chemical shift–encoded Iterative Decomposition of water and fat with Echo Asymmetry and Least-squares estimation for T2* and fat fraction quantification to assess tissue composition [71,72]; intravoxel incoherent motion (IVIM) diffusion imaging to evaluate tissue perfusion; and T1-weighted imaging to measure plantar fascia and fat pad thickness.

MRI data will be analyzed using both quantitative and qualitative approaches. Regions of interest (ROI) will be measured based on the fiducial markers corresponding to the locations identified during the clinical examination. Water and fat images will be generated using the Iterative Decomposition of water and fat with Echo Asymmetry and Least-squares estimation (IDEAL) for the separation of fat and water species [71, 72], Specifically, these will be produced using the vendor supplied chemical shift–encoded 3D gradient-echo sequence (IDEAL-IQ, GE Healthcare, WI, USA).

The IDEAL-IQ gradient-echo images will be used for marker identification and tissue segmentation, and will serve as the reference images for spatially registering the other MRI images to a common image-space. The ROIs will be delineated using the IDEAL-IQ images, guided by the locations of the fiducial markers that are superficial to the trigger points. Detailed MRI scan parameters for the foot and lower leg, respectively, are provided in Tables S1 and S2. The corresponding ROIs will then be used to measure T1ρ, T2*, perfusion fraction, and pseudo-perfusion from IVIM, as well as fat–water fractions. Measurements from each ROI will include the mean, median, and SD. Quantitative maps of fat–water fraction and T2* will be automatically generated by the scanner using the IDEAL-IQ sequence, while voxel-wise parametric maps for T1ρ, T2, and IVIM will be produced using in-house software.

Qualitative image assessments will be performed by a radiologist to exclude differential diagnoses for plantar heel pain and to confirm accurate identification of leg and foot muscles.

